# Cooled radiofrequency ablation versus cryoneurolysis of the genicular nerves for the symptomatic pain management in knee osteoarthritis: a study protocol of a prospective, randomized, single-blinded clinical trial

**DOI:** 10.1186/s13018-023-03737-1

**Published:** 2023-04-12

**Keywords:** Knee osteoarthritis, Genicular nerves, Pain, Cryoneurolysis, Cooled radiofrequency ablation

## Abstract

**Background:**

Cooled radiofrequency ablation (CRFA) and cryoneurolysis (CRYO) are two novel methods of genicular neurolysis to relief pain in symptomatic knee osteoarthritis (KOA). In this study, the two methods will be compared, giving us the opportunity to investigate their efficacy, safety and complications.

**Methods:**

In this prospective randomized trial 70 patients with KOA will be recruited using a diagnostic block of four genicular nerves. Two groups will be created through software randomization: a CRFA group (35 patients) and a CRYO group (35 patients). The target of the interventions will be four genicular nerves; the superior medial, superior lateral, inferior medial, as well as the medial (retinacular) genicular branch from vastus intermedius. The primary outcome of this clinical trial will be the efficacy of CRFA or CRYO at 2-, 4-, 12-and 24-weeks post-intervention using the Numerical Rating Pain Scale (NRPS). The secondary outcomes are the safety of the two techniques, as well as the clinical evaluation using the Knee Injury and Osteoarthritis Outcome Score (KOOS), the Oxford Knee Score (OKS), and the 7-point scale of Patient Global Impression of Change (PGIC).

**Discussion:**

These two novel techniques can block pain transmission through genicular nerves in different ways. In contrast to cryoneurolysis, the CRFA method has been well documented in the past. This is the first clinical trial to compare CRFA vs CRYO and draw conclusions about their safety and efficacy.

***Trial registration*:**

ISRCTN87455770 [https://doi.org/10.1186/ISRCTN87455770]. Registered 29/3/2022, first patient recruited 31/8/2022.

## Introduction

Knee osteoarthritis (KOA) is a degenerative joint disease that is mainly characterized by damage and loss of articular cartilage, remodeling of the subchondral bone, osteophyte formation, ligamentous laxity, weakening of periarticular muscles, and, in some cases, synovial inflammation [1]. According to Global Burden of Disease (GBD-2015 study), approximately 85% of the burden of osteoarthritis worldwide is associated with KOA [2], which has shown increased prevalence, multimorbidity, and a higher number of drug prescriptions [3]. Total knee arthroplasty (ΤΚΑ) is an effective treatment option for end-stage knee arthritis and persistent severe pain [4], but still 15–20% of the patients remain dissatisfied following this procedure; overestimated pre-operative expectations, a positive history of mental health problems, history of low back pain, and severe post-operative pain and/or suboptimal post-operative physical function are considered important factors for patient dissatisfaction following TKA [5]. However, the relatively slow progression of the knee osteoarthritis allows for stepwise algorithmic approach using non-surgical or non-pharmacological treatment options [6, 7]. Through the wide array of non-surgical treatment options, cooled radiofrequency ablation (CRFA) and cryoneurolysis (CRYO) have been proposed.

Radiofrequency ablation (RFA) is a process of thermal nerve degradation using a probe that provides radiofrequency energy. CRFA uses a water-supply system to cool the RFA probe internally. While internally cooled probes operate at a temperature of 60 °C, the temperature of the surrounding tissues reaches 80 °C, thus providing a larger lesion around the probe [8]. CRFA delivers larger and more spherical lesions compared to conventional radiofrequency ablation, thus increasing the likelihood of ablating targeted nerves; subsequently, CRFA delivers a significantly higher energy to surrounding neural tissues, which has been hypothesized to result in more durable clinical outcomes [9]. This procedure aims to disrupt the transmission of pain signals from the osteoarthritic knee via the genicular nerves. Traditionally, CRFA studies are primarily targeting three genicular nerves: the superior lateral (SLGN), superior medial (SMGN), and inferior medial (IMGN). Some reports also include the medial (retinacular) genicular nerve from vastus intermedius (MRGN) [10, 11].

Cryoneurolysis involves the application of cold temperatures (− 20 to − 100 °C) to a peripheral nerve, leading to Wallerian degeneration and subsequent analgesia, while the nerve retains its ability to regenerate [12–16]. In contrast to CRFA which completely ablate the targeted nerve, CRYO has the ability to disrupt nerve function while structural elements of the nerve bundle remain intact. This allows for complete regeneration and functional recovery of the nerve over time. CRYO studies, so far, are primarily targeting the infrapatellar branch of the saphenous nerve (IPBSN), a sensory nerve that innervates the anterior and inferior parts of the knee capsule and/or the anterior femoral cutaneous nerve (AFCN) [13, 14, 16]. The CRYO probe that will be used in this study (IceSphere 1.5 CX, Galil Medical Ltd) creates also a spherical lesion of ice around the tip thus increasing the likelihood of degenerate the targeted nerves.

Clinical evidence in general, suggests that both CRFA and CRYO are safe and effective procedures for the symptomatic management of KOA pain [11–18].

The primary objective of our proposed trial is to evaluate the efficacy of CRFA or CRYO at 2-, 4-, 12- and 24-weeks post-intervention in patients with painful KOA using the Numerical Rating Pain Scale (NRPS).

The secondary objectives are the comparison of safety and tolerability of the two interventions, as well as the patient’s clinical outcome at 12- and 24-weeks post-intervention, using the Knee Injury and Osteoarthritis Outcome Score (KOOS) and the Oxford Knee Score (OKS). Also, the 7-point scale of Patient Global Impression of Change (PGIC) will be used at 2-, 4-, 12-, and 24-weeks post-intervention to capture the patients’ feelings of improvement.

## Methods

This study protocol describes the design of a prospective, single-blinded RCT with an allocation ratio of 1:1, between CRFA and CRYO. Our main hypothesis is that substantial relief of pain would be achieved with both techniques (CRFA and CRYO) compared to baseline values and that both methods would be effective and tolerable in the intermediate management of KOA. (Fig. 1).

**Fig. 1 Fig1:**
[figure not shown]
Flowchart of the study

### Study setting

The study will be conducted at the Department of Orthopaedics, University Hospital of Patras, Greece. The institutional review board (IRB) of our University Hospital has approved the study (11846/05/10/2021), and written informed consent from participating patients will be obtained. The study will be conducted in accordance with all applicable laws and regulations as specified in the International Conference on Harmonization Guideline for Good Clinical Practice and the Declaration of Helsinki.

### Eligibility criteria

After establishing the diagnosis of knee osteoarthritis according to the eligibility criteria outlined below, the patients will visit the Department for initial clinical assessment and diagnostic block of the genicular nerves**.** Patients will be asked to rate the percentage of their knee pain according to NPRS while performing ambulation, squatting, and other maneuvers that typically provoke their pain during the next 30 min in the office. After the diagnostic block of the six main anatomical sites described below the patients will then be asked to rate any reduction in their knee pain while performing the same maneuvers in the office. The primary investigators will rate these results and decide on their eligibility. Patients will be only enrolled in the study if they report, at least 50% reduction in pain (as measured in the NRPS). Eligible patients will be then randomizing as 1:1 to either CRFA or CRYO. Participants with bilateral KOA will not be excluded; only one knee will be screened and enrolled as the “index knee” for treatment.

Patients of either sex can participate in the clinical trial if they have:the NICE clinical criteria [19] of primary KOA for one or both knees: as follows: (a) age > 45; (b) activity-related joint pain and (c) no morning joint stiffness or morning stiffness that lasts no longer than 30 min.Radiological confirmation of knee arthritis (grade ≥ 2) according to the Kellgren and Lawrence classification [20].Chronic knee pain for a minimum duration of 6 months.Pain intensity ≥ 4 on the (NRPS).A decrease of ≥ 50% in NRPS scores with diagnostic genicular nerve block.The ability to communicate in Greek.

### Exclusion criteria

Patients who belong to any of the following groups will be excluded:Inflammatory or posttraumatic knee arthritisPatients who received CRYON or CRFA treatment in the pastInjection of hyaluronic acid, PRPs, or corticosteroids within the previous 3 monthsSignificant structural deformities affecting locomotion and knee function asidefrom osteoarthritis and which might cause chronic knee painBody mass index ≥ 40 kg/m^2^Uncontrolled serious diseases (cancer, diabetes, end-stage heart disease, etc.)Unstable psychiatric illnessesCoagulopathy or bleeding disordersActive systemic or local infectionsDisease associated with reactions to the cold, such as cryoglobulinemia

Patients who fulfill the inclusion criteria will be then informed about the proposed treatment options (CRFA or CRYO). The current literature on CRFA has shown promising results for pain relief up to 12 months (11,17,18), whereas data are scarce for CRYO (13,14,16) which has been less investigated thus far. Treatment with cryoneurolysis is still in its early stage and further studies are needed to determine methodological strategies optimizing its potential therapeutic effects. Nyggard et al. [14] have recently (2021) published a study protocol that aims to compare cryoneurolysis + standardized education and exercise vs sham group + standardized education and exercise; in this study the ICEfx technology will be used, as in our study, but the targeting nerves would be different (the infrapatellar branch of the saphenous nerve (IBSN) and the anterior femoral cutaneous nerve (AFCN)). The extent of nerve damage depends on several factors including temperature, contact area, freezing rate, exposure time and thawing strategy. Our study would apply a specific freezing protocol, similar to Nyggard et al. [14], that is relatively short (3 min), utilizing a single freezing cycle and not at full effect (slower freezing). This might reduce potential risks associated with the procedure but might also attenuate treatment effects.

### Intervention description

#### Initial assessment

The baseline assessment will include: (a) the medical history of the patient (age, sex, body mass index, duration of pain, comorbidities, use of analgesics, and prior interventions of the knee joint); (b) radiological classification using standing AP and lateral x-rays of the knee joint and (c) baseline clinical evaluation using the NRPS, OKS, and KOOS. The OKS is a 12-item patient-reported outcome score, specifically designed and developed to assess function and pain after total knee replacement (TKR) surgery [21]. It is valid, reproducible, and sensitive to clinically important changes without a ceiling or floor effect for both its pain and function subscales [22]. The OKS has been translated and validated for Greek patients with knee osteoarthritis [23]. The KOOS questionnaire was developed in the 1990s as an instrument to assess the patient’s opinion about their knee and associated problems [24]. KOOS score has 5 subscales; Pain, other Symptoms, Function in daily living (ADL), Function in sport and recreation (Sport/Rec) and knee related Quality of life (QOL). KOOS includes WOMAC Osteoarthritis Index LK 3.0 in its complete and original format (with permission), and its convergent and divergent construct validity has been determined in multiple studies in comparison to several instruments including the different subscales of SF-36 and the Lysholm knee scoring scale [25]. The KOOS questionnaire has been translated and validated for Greek patients with total knee replacement [26].

Patients who fulfill the inclusion criteria and have no exclusion criteria will be informed about the clinical trial in detail, and a consent form will be required to proceed.

### Targeting of the nerves (for diagnostic block or final intervention)

Precise targeting of genicular nerves using fluoroscopic guidance is mandatory for a successful procedure. Most of the current CRFA studies are using the classic radiological targets proposed by Choi et al. [27], McCormick et al. [28] and Conger et al. [29] aiming for the SLGN and SMGN at the junction of the midpoint of the femoral shaft and the lateral/medial femoral condyle whereas for the IMGN at the junction of the midpoint of the tibial shaft and medial tibial condyle. However, recent anatomic and dissection studies have suggested different target points especially for the SLGN and SMGN [30–33] and have proposed supplementary or totally different landmarks for precising targeting.

In the current study the target of the diagnostic block or final intervention will be the SMGN, the SLGN, and the IMGN, as well as the medial (retinacular) genicular branch from vastus intermedius (MRGN) (Fig. 2). For the SLGN we will use two landmarks: the classical one at the confluence of the femoral shaft and the lateral femoral condyle in the AP view and the midpoint of the femur width in the lateral view [27–29] but also the new proposed landmark from Fonkoue et al. [31] that is located more distal (closer to lateral epicondyle) in the AP view and laterally in the area connecting the posterior cortex of the femur shaft and the superior edge of the lateral condyle. Similarly, for the SMGN the classic point at the confluence of the femoral shaft and the medial femoral condyle in the AP view and the midpoint of the femur width in the lateral view will be used first followed by the new landmark [31] located more distal and closer to adductor tubercle (AT) in the AP view and just few millimeters anterior to the AT in the lateral view. The IMGN will be targeted at the concave transition between the tibial plateau and adjacent metadiaphyseal shaft in the AP view and at the midpoint of the tibia shaft in the lateral view [27–31]. Finally, the MRGN will be located at the middle of the AP distance of the femur, 3–4 cm above the superior patella pole, as has been described by Wong et al. [11].

**Fig. 2 Fig2:**
[figure not shown]
**a, b** Anteroposterior and lateral radiographs of an arthritic knee showing the intended target-points of the genicular nerves (M1, M2 = SMGN, M3 = IMGN, L1, L2 = SLGN, L3 = MRGN); **c** intraoperative picture of the needles in the lateral side just prior to ablation **d** anteroposterior and lateral fluoroscopic images of the exact location of the needles in the lateral side; **e** intraoperative picture of the needles in the medial side just prior to ablation; **f** anteroposterior and lateral fluoroscopic images of the exact location of the needles in the medial side

For the nerve blocking procedure 1–2 ml of 2% lidocaine would be injected in the six different areas that mentioned previously, and the patients will then be asked to rate the percentage reduction in their knee pain while performing ambulation, squatting, and any other maneuvers that typically provoke their pain during the next 30 min in the office. Patients with a reduction in pain (> 50%) will proceed to the next phase, whereas those who experience no change in perceived pain will be excluded from the clinical trial.

### Intervention

Patients will be placed in the radiolucent table at the Department of Interventional Radiology in a supine position with a bolster under the knee to produce 30° of flexion; this position flattens the suprapatellar joint space, thus minimizing needle trespass, and also allows for an unobstructed lateral view of the knee. The treated knee will be draped and sterilized in a standard manner. Patients will be continuously monitored and administered conscious sedation (1–2 mg IV midazolam and/or fentanyl 25–100 mcg IV) and supplemental oxygen. Fluoroscopic images will be obtained to align the femur in an anteroposterior (AP) view in order to target the genicular nerves at locations above the femoral condyles and for the IMGN a greater caudal tilt of the fluoroscope will be obtained to square off the tibial plateau for an appropriate AP view. A sealed and opaque envelope will be brought to the operating theatre, dictating the group of each patient. The location of the nerves (SLGN, SMGN, IMGN, and MRGN) will be identified using fluoroscopy**,** according to previously described methods.

### CRFA technique

Two to 3 ml of 1% lidocaine is used to anesthetize the skin and subcutaneous tissues before cannula insertion at each target site under fluoroscopic guidance. Thereafter, a 50–150 mm 17-gauge introducer needle will be placed to ablate the SLGN, SMGN, IMGN, and MRGN. One milliliter of 2% lidocaine will be injected through the introducer needles to anesthetize the area before ablation. After placement of the introducer needle, a 18 gauge, internally cooled 4-mm active tip RFA electrode (Coolief, Halyard Health, Alpharetta, GA, USA) will be placed into the introducer needle, and the positioning is checked again using fluoroscopy. The introducer is connected to COOLIEF* Cooled RF Advanced Generator that allows staggered start, stop and adjusting of 4 independent channels. Motor nerve activity will be excluded by testing at 2 Hz and 1 mA. The CRFA probes will be advanced, and ablation will be performed with lesion settings at 60 °C (80–90 °C adjacent tissue temperature) for 2.5 min. As mentioned before, this type of ablation creates a spherical lesion at the tip of the probe. Cooled RF electrodes include a thermocouple at the active electrode tip to provide a temperature-controlled lesion formation. This involves water-cooling of the active electrode tip during the duration of the process without tissue charring at the electrode tip; this mechanism doubles the lesion radius and increase the lesion volume by 5 times.

#### CRYO technique

Two to 3 ml of 1% lidocaine is used to anesthetize the skin and subcutaneous tissues before probe insertion at each target site under fluoroscopic guidance. A cryoneurolysis probe (ICESphere 1.5 CX, Galil Medical Ltd.) will be inserted in the proximity of the six target points, guided by fluoroscopic visualization, as previously described. VisualICE generator (Galil Medical Ltd.) will be used for cryoneurolysis which utilizes Argon as a coolant and Helium to thaw. The procedure will be performed with a single freeze cycle: 30 s at an effect of 20% and 2 min 30 s at 60% effect. After freezing cycle, 1 min of active thaw and 1 min of passive thaw will be used. As mentioned before the CRYO probe creates a spherical lesion (ice-ball) that surrounds the active tip. The temperature gradient away from the probe increases importantly; the typical isotherm with the needle has a temperature of − 40 °C in an area equivalent to 15 × 23 mm. Already at 23 × 29 mm the temperature has risen to − 20 °C and at 33 × 37 mm the temperature is up to 0 °C. The thawing phase (2 min) is not considered active treatment but is necessary for the ice-ball to melt gradually for later safe removal of the probe. The active ablation time of CRYO (3 min) is similar to that of CRFA (2.5 min) but with a different mechanism. The area of ablation is spherical in both techniques thus increasing the probability that a targeted sensory nerve will be captured in the “sphere” of tissues neuroablated. Finally, the “slow” effect of freezing (20% for 30 s and 2 min 30 s at 60%) has been already proposed for genicular nerve ablation [14] in patients with KOA and is considered less destructive as it aims on Wallerian nerve degeneration than nerve tissue destruction. In other more severe cases (primary tumors, metastases) the CRYO technology is used at higher effect levels, larger areas of ablation with several probes inserted and also repeated cycles of freezing.

Patients will discontinue all pain medications (opioids, NSAIDS, anti-depressants and anti-convulsant drugs), supplements, chondroprotective drugs, and other alternative therapies for KOA for 10 days prior to the screening/baseline visit. During follow-up, patients will be prohibited from undergoing any other adjunctive treatment for KOA, including steroid injections, viscosupplementation, and pain medications. Serious local complications from either CRFA or CRYO and the need for medications for pain relief will be a criterion for study discontinuity.

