### Outcomes

Patients will be assessed at baseline and 2-, 4-, 12-, and 24-weeks post-intervention (Table 1).

**Table 1 Tab1:** Timeline of the study

Timepoint	Enrollment		Allocation		Assessment times		
	− 3 w	− 1 w	0 w	2w	4 w	12 w	24 w
Enrollment							
Eligibility screening	√						
Informed consent	√						
Genicular nerve block		√					
Allocation			√				
Outcome measures							
NPRS (primary)			√	v	√	√	√
KOOS			√	–	v	√	√
OKS			√	–	v	√	√
PGIC			–	–	v	√	√
Complications medications			Intra-op				
			√	v	√	√	√
			√	v	√	√	√

*NPRS* Numerical Pain Rating Scale, *KOOS* Knee Injury and Osteoarthritis Outcome Score, *OKS* Oxford Knee Scores, *PGIC* Knee Patient Global Impression of Change

The primary outcome would be the efficacy of CRFA or CRYO at 2-, 4-, 12- and 24-weeks using the Numerical Rating Pain Scale (NRPS). The secondary outcomes will be the potential improvement of the KOOS, and OKS at 12- and 24-weeks post-intervention. Patients will be also asked about their impression of improvement using the 7-point scale of Patient Global Impression of Change (PGIC) [34]; PGIC responders are the patients who indicate that they are either “very much improved” or “much improved” at each follow-up assessment. Expected side effects and complications (for example, bruising, swelling, numbness, inflammation, and/or erythema) involving percutaneous access to the nerves and the use of local anesthesia will be assessed at each follow-up visit and documented independently, except for loss of motor function outside the treatment area. The details of the timeline, assessments, and follow-up evaluations are presented in Table 1.

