### Strengths and limitations

This will be a single-blinded randomized control trial with a follow-up period of six months. The strengths are the recruitment of enough patients to demonstrate a statistical significance of 90%, the precise targeting of the nerves in six different areas in accordance with old proven clinical reports and the new landmarks provided by recent anatomical studies and also that both techniques (CRFA and CRYO) would be applied at the same manner. Technical limitations also exist, as the effectiveness of these treatments relies heavily on accurate spotting of the genicular nerves and also from the fact that we are not able to spot all the nerves of the knee joint capsule. The extent of nerve damage and its capacity to regenerate also depends on parameters that cannot be fully controlled in this clinical trial. CRFA has a different mechanism of action (thermoablation with permanent? nerve damage) compared to CRYO that provokes cryoablation with Wallerian degeneration. This might reduce potential risks associated with the CRYO procedure but might also attenuate treatment effects. If CRYO turns out to be more effective or safer than CRFA would be probably considered as a novel non-pharmacological option for KOA that would be covered by medical insurances in the future.

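### A serious local complication ends a patient's participation although treatment is already complete, so the event's course and any later events to week 24 go unrecorded

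*Protocol article*

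**What the plan says.** The discontinuation rule stands in the last paragraph of the CRYO technique section, but it names both procedures and so applies to both arms: "Serious local complications from either CRFA or CRYO and the need for medications for pain relief will be a criterion for study discontinuity".

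Treatment is given once. In the CRFA arm, "ablation will be performed with lesion settings at 60 °C (80–90 °C adjacent tissue temperature) for 2.5 min". In the CRYO arm, "The procedure will be performed with a single freeze cycle: 30 s at an effect of 20% and 2 min 30 s at 60% effect". Table 1 places allocation at week 0 and shows no later treatment session.

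Safety is a stated aim. The Abstract says "The secondary outcomes are the safety of the two techniques", and the Introduction says "The secondary objectives are the comparison of safety and tolerability of the two interventions". Under Outcomes, expected side effects and complications "will be assessed at each follow-up visit and documented independently". Table 1 puts these assessments at 2, 4, 12 and 24 weeks, besides the intra-operative record.

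Three other places touch on serious events or retention:
- Implementation and blinding provides for unblinding after severe adverse effects.
- Data collection and management covers missed appointments and refusals to attend, and rules out further retention efforts.
- Interim and additional analyses lists serious complications as a reason to stop the trial.

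**The concern.** A rule that takes a patient off treatment after a complication is ordinary where treatment continues. Here the ablation is over on the day it is given. A patient-level exit triggered at, say, week 2 changes nothing about exposure to the study intervention. It only removes the visits at which the event's course would be documented.

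The trial sets out to compare the safety of two neurolytic techniques over 24 weeks. For a serious local complication, the informative question after its occurrence is whether it resolved, and when. Under the rule as written, the trial stops looking at that point in exactly those patients. With a planned 35 per arm, one patient is 1/35 = 2.9% of an arm, so a few unresolved histories can leave the comparison of lasting harm undecided.

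**Working it through.** No figure in the plan is in dispute. The check is a reading of the passages, followed by simple counting.

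**1. Is the rule about a patient or about the trial?** The sentence joins serious local complications to the need for pain medication, which can only describe an individual. It follows two sentences on what patients must stop or avoid. Trial-level stopping has its own rule under Interim and additional analyses. The patient-level reading is therefore the natural one.

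**2. What can the rule stop?** Both technique sections describe one session, and Table 1 schedules no second one. Once the session is complete, only follow-up remains.

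**3. Does it conflict with another section?** Outcomes and Table 1 require complications to be assessed at each visit to week 24. A patient discontinued under the rule would not reach the remaining visits. Both statements cannot hold for that patient.

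**4. Does another section rescue the follow-up?** Unblinding does not keep a patient in the study. The retention measures deal with missed appointments and refusals, not with patients whom the protocol itself discontinues. No other provision was found.

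**5. What is lost per patient?** There are 4 follow-up visits (weeks 2, 4, 12 and 24). Visits lost by time of exit:
- before week 2: 4 of 4
- at week 2: 3 of 4 (75%)
- at week 4: 2 of 4 (50%)
- at week 12: 1 of 4 (25%)

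**6. What might be lost in total?** The documents give no serious-complication rate, so the rates below are assumptions. Expected leavers = 70 × rate. Visits lost if all leave at week 2 = 3 × leavers.
- 1%: 0.7 leavers, 2.1 visits
- 3%: 2.1 leavers, 6.3 visits
- 5%: 3.5 leavers, 10.5 visits
- 10%: 7 leavers, 21 visits

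The full schedule is 70 × 4 = 280 visits. The loss is small in number but falls entirely on patients with serious events.

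**7. What survives and what does not?** Suppose 2 of 35 patients in one arm have a serious nerve injury found at week 2 (an assumed count). The number ever affected is 2/35 = 5.7% with or without the rule, because the event has been detected and recorded. If both patients leave, their week-24 status is unknown: persistent injury could be anything from 0/35 (0%) to 2/35 (5.7%). With follow-up kept, it would be known.

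**The case against.** The strongest reply is that the article speaks only of study discontinuity and never says that visits or complication recording cease. What happens to a patient after discontinuation is a detail that a fuller protocol may hold. This stands as a limit on certainty. It does not dispose of the point, because the published sentence, in its plain meaning, contradicts the published visit schedule, and a reader applying it would stop follow-up.

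The objection also rightly blocks several stronger readings that a reader might infer:

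- *That persistent harm would be reported as zero.* In the example above, counting only week-24 attenders would give 0/33, with an exact two-sided 95% upper limit of 1 − 0.025^(1/33) = 10.6%. But the protocol defines no such week-24 prevalence and nowhere says that complications are counted only in those still attending. The count of patients ever affected is preserved.
- *That these patients alone carry the safety comparison.* The examples under Outcomes are bruising, swelling, numbness, inflammation and erythema. Patients with such events stay in unless the event is a serious local complication.
- *That the rule removes the patients in whom the arms' difference in reversibility could be seen.* The limitations section says "CRFA has a different mechanism of action (thermoablation with permanent? nerve damage) compared to CRYO that provokes cryoablation with Wallerian degeneration", and the Introduction describes nerve regeneration after CRYO. Both are about mechanism, and the Introduction's regeneration concerns the targeted nerves, not recovery from an unintended injury. Recovery of targeted nerves concerns all treated patients, most of whom the rule need not touch.
- *That one arm is favoured.* The rule is the same in both arms. Loss of information would be unequal only if serious complications were, and the documents give no rates.

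The protocol also expects no discontinuation from the intervention. That bears on how often the rule would be used, not on whether it is sound.

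**Conclusion.** The point holds in limited form. As written, a patient with a serious local complication leaves the study although no study treatment remains to be stopped. This contradicts the schedule of complication assessments to week 24 and works against the secondary safety objective. The number of patients with a serious complication per arm is not affected. The resolution or persistence of the event, and any later events, are lost: 3 of 4 follow-up visits for an exit at week 2, and between 1 and 4 for exits from week 12 back to before week 2.

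The conclusion assumes that the rule operates on the individual patient and that discontinuity means the end of scheduled visits. Both are the plain reading; the second is not spelled out. The total size is unknown. Severity is moderate: a secondary outcome is affected, but visits not made cannot be recovered later.

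**What to change.** Reconcile the discontinuation sentence with the Outcomes section and Table 1 by separating discontinuation from follow-up:

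- State that a patient who meets the complication criterion remains under scheduled outcome and safety data collection to week 24 unless consent is withdrawn.
- Record the outcome of each such event (for example resolved, resolving or persistent) with its date.
- Report complications in all treated patients by arm, with the number actually treated as denominator (planned 35), not only in those still attending.
- Leave trial-level stopping for serious complications where it is, under Interim and additional analyses.

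The cost is one protocol sentence and one field on the existing paper form, since the visits are already scheduled. The change concerns data collection only; how a complication is managed clinically is not addressed here.
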